#### 7.4.1 Preparation/handling/storage/accountability

Drugs should be stored at room temperature (<30°C) protected from direct sunlight, as per package insert. Records must be maintained that document receipt, release for dosing, disposal, or return to the Sponsor.

#### 7.4.2 Strategies to improve adherence to study protocol monitoring adherence

##### 7.4.2.1 *Adherence to study protocol and medication*

Where feasible, study participants will be reminded about any follow-up visits through mobile phone contact. All information will be recorded on the appropriate sections of the CRF. Subjects judged to be non-compliant may continue in the study but will be counselled on the importance of taking their study medication as prescribed or following the study's follow-up schedule. Participant initiated consultation via text messaging, or mobile phone calls will be available to provide support to the participant to complete study procedures.

##### 7.4.2.2 *Strategies for retention*

During screening and consent procedures, potential participants will be asked whether they live in the catchment area, are willing to adhere to the study protocol. Specifically, potential participants who will be eligible to self-isolate at home according to the local Government's guidelines in each country will be asked whether they will be willing and able to comply with the frequent follow-up schedule. The 'study catchment area' will be defined for each study site before the start of the study. Dedicated study transport will be arranged for follow-up visits. All participants who make their own travel arrangements, e.g. for unscheduled/unannounced sick visits, will be reimbursed for transportation costs to and from the clinic.

GPS position and otherwise, detailed directions to participants' homes as well as contact information, including mobile phone information, will be recorded at enrolment. The study team will call participants daily in between scheduled visits. For scheduled follow-up visits study transport will be arranged. If participants cannot be reached by mobile phone, study staff may visit their house to help arrange transport to the clinic if the participants are willing to come to the clinic, or, alternately, a study staff member may go to their home for clinical evaluation and assess if they still wish to participate in the study. All information will be recorded on the appropriate sections of the CRF. Subjects judged to be non-compliant may continue in the study but should be counselled on the importance of taking their study medication as prescribed.

##### 7.4.2.3 *Adherence to study drug*

If participants are eligible to self-isolate at home, the first dose of each 3-day course will be given under the supervision of study staff and the remaining doses for day-1 (AL), days 2 (AL or PA) and 3 (AL or PA) will be taken at home by the study participants. All participants in this nested malaria treatment trial will be contacted by mobile phone to take the assigned tablets or sachets. If

participants are admitted to isolation wards, the subsequent doses will be given as directly observed therapy by study staff or ward nurses. Details of the time of the dose and adherence monitoring will be recorded on CRFs. If adherence to the prescribed antimalarial treatment regimen is in doubt and/or the correct number of tablets or sachets of the study drug was not taken, an explanation of the reason why the treatment was not followed will be recorded on the case report form where possible.

### 7.4.3 Permitted and prohibited concomitant medication and care

#### 7.4.3.1 Routine care

Care and management of confirmed COVID-19 patients will be done in line with the COVID-19 National Guidelines which in Kenya and Burkina Faso currently includes isolation for treatment for those testing positive at designated isolation centres approved by the MoH, or self-isolation and home-based care, as well linkage to the contact tracing teams at the MoH offices to facilitate testing of primary contacts. This includes analgesic for fever and other symptoms and haematinics for participants with evidence of anaemia.

#### 7.4.3.2 Concomitant therapy documentation

Participants will be asked about concomitant medications at the screening/baseline evaluation visit. Participants will be counselled to avoid concomitant medications not prescribed by the study clinic, specifically antimalarial drugs. During the study, participants will be asked to complete surveys (Daily Survey and Exit Contact Survey) that include information regarding any medication or vaccine (including over-the-counter or prescription medicines, vitamins, and/or herbal supplements) that the participant receives during the study. At each contact, the Investigator will also question the participant about any medication taken. All concomitant medications taken during the study will be recorded in the appropriate sections of the CRF with indication, dose information, and dates of administration.

All medication used for the management of COVID-19 is permitted, with the exceptions listed under section 7.4.3.3, Prohibited medication, page 38. For COVID-19 participants with malaria who are enrolled in the nested malaria treatment trial, permitted medication includes the use of azithromycin. Other permitted medication includes artesunate or quinine for severe malaria, standard treatments for co-infections (e.g. soil-transmitted helminths, TB, HIV, schistosomiasis, etc.), antibiotics for suspected bacterial infections, haematinics for anaemia, antipyretics/analgesics (e.g. paracetamol, ibuprofen) and treatment for other symptoms as appropriate.

#### 7.4.3.3 Prohibited medication

Prohibited medication for participants enrolled in the treatment study, includes other antimalarial drugs not prescribed within the trial protocol (e.g. chloroquine, amodiaquine), or local remedies that have antimalarial activity, such as herbal remedies containing extracts from the *Artemisia annua* plant (sweet wormwood) used in a tonic against COVID-19 in Madagascar, Tanzania, Chad, and Togo. Randomised participants who take prohibited medications resulting in the premature cessation of the study intervention, will remain in the trial and will be included in the primary, intention-to-treat analysis, but excluded from the per-protocol analysis.

#### 7.4.3.4 Precautionary medications

Use of medications classified as precautionary is not considered as prohibited but will be discussed with the study clinician and the participant.

#### 7.4.3.4.1 Artemether-lumefantrine

Precautionary medications include drugs that are known to prolong the QT interval. Drugs that have a mixed effect (inhibitors and inducers) on CYP3A4, especially antiretroviral drugs such as HIV protease inhibitors and non-nucleoside reverse transcriptase inhibitors, and those that have an effect on the QT interval should be used with caution in patients taking artemether-lumefantrine. Artemether-lumefantrine may reduce the effectiveness of hormonal contraceptives. Therefore, patients using contraceptives should be advised to use an additional non-hormonal method of birth control.

### 7.4.4 Treatment after the end of the study

No additional treatment will be provided at the end of the study.

## 8 DISCONTINUATION/WITHDRAWAL CRITERIA

### 8.1.1 Discontinuation of study treatment

Study treatment for those enrolled in the nested malaria treatment trial will be discontinued for the following reasons:

- Hospitalisation (at the discretion of the inpatient provider, hospitalised participants may continue to receive study treatment if maintained on the originally randomised treatment regimen)
- The requirement for prohibited concomitant medications or other contraindication to study product
- The occurrence of an AE requiring discontinuation of study product, even if not addressed in Section 7.2, page 34
- Request by a participant to terminate study treatment

Participants who stop study product should continue the study participation off study product with continued evaluations as per the Schedule of Activities. The reason for study product discontinuation should be recorded.

Hospitalised participants will be followed through hospitalisation.

### 8.1.2 Withdrawal from the study

- A participant may withdraw from the study at any time at his/her own request or may be withdrawn at any time for the following reasons:

- At the request of the primary care provider if he/she thinks the study is no longer in the best interest of the participant
- A participant is judged by the Investigator to be at significant risk of failing to comply with the provisions of the protocol as to cause harm to self or seriously interfere with the validity of the study results
- At the discretion of the Institutional Review Board/Ethics Committee or government agencies as part of their duties, Investigator, or industry supporter
- If the participant withdraws consent for disclosure of future information, the Sponsor may retain and continue to use any data collected before such withdrawal of consent.
- If a participant withdraws from the study, he/she may request destruction of any samples taken and not tested, and the Investigator must document this in the site study records. If the request is received after the dataset has been anonymised, the stored sample can no longer be withdrawn.
- See for data to be collected at the time of study discontinuation and follow-up and for any further evaluations that need to be completed.

### 8.1.3 Lost to Follow-up

A participant will be considered lost to follow-up if he/she is unable to be contacted by the study site while taking the following actions into account:

- The site must attempt to contact the participant as soon as possible and counsel the participant on the importance of maintaining the assigned procedure schedule and ascertain whether or not the participant wishes to and/or should continue in the study.
- Before a participant is deemed lost to follow-up, the Investigator or designee must make every effort to regain contact with the participant (where possible, three telephone calls and, if necessary, a home visit to the participant's last known place of residence). These contact attempts should be documented in the participant's case record forms.
- Should the participant continue to be unreachable, he/she will be considered to have withdrawn from the study with a primary reason recorded as 'lost to follow-up'.

## 9 PARTICIPANTS TIMELINE AND STUDY ENCOUNTERS

---

The current COVID-19 pandemic has placed a significant burden on the healthcare system. For this study, specimen and data collection will be conducted to minimise the impact of asymptomatic or paucisymptomatic participants within the healthcare system. If the participant is assessed as eligible, direct contact between study participants and study personnel will be minimised, and we will make use of mobile phone and text message as much as possible during the follow-up period on days that biological sampling is not indicated.

Participants will be instructed to contact the study staff by phone as soon as possible should they manifest signs or symptoms of LRTI or if their clinical situation worsens. They will also be instructed to notify any non-study health care personnel about trial participation if they seek care from non-study clinics.

### 9.1 SCREENING STUDY (CROSS-SECTIONAL SURVEY SOURCE POPULATION)

Most of the source population data and procedures will be collected and conducted by routine staff as part of the local response to the COVID-19 epidemic. Basic demographic, medical and travel histories will be taken, the approximate location of residence determined, and a basic physical

examination performed. Any relevant demographic or health-related information will be copied from existing hospital and clinic records. The contact telephone numbers and location of residence will be recorded for all participants.

As of writing (July 2020), most suspected cases, including those with mild or no symptoms, are admitted for at least one day on the quarantine/isolation wards of the local referral hospitals until the results of the COVID-19 test are known. It is expected that this may change during the course of the pandemic (and thus the study) when hospital isolation wards reach capacity when it is anticipated that Government guidelines in each country will allow or encourage self-quarantine or self-isolation at home and home-based care while waiting for the COVID-19 test results, which are typically available within 18 to 48 hours, although this may vary during the course of the pandemic.

### 9.1.1 Pre-screening with point of contact (POC) SARS-CoV-2 antigen tests

The screening study (cross-sectional survey, source population) includes pre-screening with an experimental POC SARS-CoV-2 antigen tests and Government approved antigen tests. At the time of writing (September 2020), there are no approved SARS-CoV-2 antigen tests yet in Kenya or Burkina, but this may change during the course of the study. We will follow the national guidelines in each country. In Kenya GeneXpert, antigen-RDT and PCR results are considered for definitive diagnosis of COVID-19. If a participant tests COVID positive for any rapid antigen tests, GeneXpert, or PCR, the participant shall be enrolled.

Eligible patients with both a positive SARS-CoV-2 test and a positive malaria test on Day-0 require malaria treatment that same day and will be invited to enrol in the COVID-19 cohort study and the nested malaria treatment trial on Day-0; i.e. prior to knowing the SARS-CoV-2 PCR results (see 9.2.1.3, Nested malaria treatment trial, page 43). Patients with a positive antigen test but negative for malaria will be invited to participate in the COVID-19 cohort study and can choose whether to enrol that same day (Day-0) or wait until the confirmatory PCR results become available (typically on Day-1).

### 9.1.2 Healthy controls

In addition to enrolling those with COVID19 into the cohort, approximately 100 healthy control participants (~ 50 per country) will be invited to provide a venous blood sample (5 mL) at a single timepoint. These will be individuals identified through the screening study (cross-sectional survey, source population) and will be SARS-CoV-2 antigen RDT negative (nasal swab) and Plasmodium antigen-negative (finger prick) and will have no symptoms at the time. Where such individuals have been identified retrospectively within the previously screened population, they will be contacted and invited to repeat the rapid tests to confirm their COVID-19 and malaria-free status before providing a venous blood sample. If they have received a COVID-19 vaccine, this should be at least four weeks before the samples are taken.

Venous blood (5 mL) from those who consent will be taken into an EDTA tube and a PAXgene tube to correspond with samples from COVID-19 cohort participants.

Venous blood from healthy control participants will be used for the systems immunology component investigating T and B cell markers and for transcriptional profiling as a comparison/control group against the COVID-19-malaria negative and the COVID-19-malaria positive patients.

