- a Screening for Covid-19 as part of a screening study (cross-sectional survey, source population). Screening and Day 1 evaluations may occur on the same day if the point of care antigen SARS-CoV-2 tests result is positive. This depends on the malaria status of the patient (i.e. malaria positive: Invite eligible participants to enrol in the nested malaria treatment trial on Day-0; malaria-negative: Provide the participant with the option to enrol in the COVID-19 cohort study either the same day (Day-0) or wait until the confirmatory PCR results are available on Day-1 (see e, below)). A sub-group of participants who test negative by both SARS-CoV-2 antigen RDT and malaria RDT, and are feeling well, will be invited to participate as healthy controls.
- b These evaluations will be conducted by telephone and/or text messaging
- c These evaluations will be conducted among participant enrolled in the nested malaria treatment trial only
- d Any default diagnostic swab performed by local health authorities is acceptable. Additional swabs will be taken for a SARS-CoV-2 point of care antigen test.
- e The number of days for the SARS-CoV-2 test results to become available can be longer than 1 day and may vary by site.
- f Blood sample for SARS-CoV-2, malaria diagnostics and malaria and non-malaria serology in source population (fingerpick, 250 µL dried blood spot and malaria RDT). Consenting healthy control participants will provide a single 5 mL venous blood sample for CyTOF for B and T cell markers (fixed whole blood), Olink immunoassay (plasma) and transcriptional profiling (gene expression).
- g Saliva sample (~1mL) for SARS-CoV-2 RNA and antigen detection and SARS-CoV-2 and malaria serology
- h Includes questions for the WHO Ordinal Scale for Clinical Improvement and/or modified Flu-PRO PLUS
- i Daily during the first 14 days, or until the participant is asymptomatic for two consecutive days, whichever comes last, and then on days 21, 28 and 42
- j Mid-nasal swabs for research specific molecular detection and viral load and sequencing of SARS-CoV-2 (for later batch analysis, not for patient care)

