### 7.3 METHOD OF TREATMENT ASSIGNMENT

Balanced randomisation will be used using permuted block randomisation methods stratified by site (i.e. hospital or clinic) and by the presence of symptoms at enrolment consistent with COVID-19 (asymptomatic vs symptomatic). A statistician in the UK will generate the randomisation lists with the allocation sequence, which will be forwarded to the trial pharmacists based in Kenya and Burkina Faso who will then prepare sequentially numbered, sealed, opaque boxes or envelopes for each participant with the randomisation assignments. Contained within each of these envelopes or boxes will be the pre-packed investigational product. The opaque boxes/envelopes will be opened sequentially upon enrolment of a study participant in each site. Stratification by the presence of symptoms at enrolment is needed to ensure balanced distribution among the two study arms as the presence of symptoms is likely to be an important (known) predictor of the COVID-19 disease progression (the primary endpoint). Currently at least half of the COVID-19 cases identified in Kenya are asymptomatic, reflecting targeted screening of contacts and high-risk populations. Minimisation or distance randomisation using central randomisation services by internet is not feasible because of the unreliable internet connections and telephone services in some of the proposed sites.

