#### 10.2.2 Blood samples

During the screening study (cross-sectional survey, source population) a fingerprick blood sample (about 250 µL) will be taken for malaria diagnosis by malaria RDT, malaria microscopy and a dried blood spot for malaria PCR, and for SARS-CoV-2, malaria and non-malaria serology. Approximately 100 healthy control participants (~ 50 per country) who test negative by SARS-CoV-2 antigen RDT during screening and are malaria RDT negative will have a 5 mL venous blood sample taken.

In the participants enrolled in the COVID-19 cohort study, whole blood will be stored in PAXgene Blood RNA Tubes, which inactivates and stabilises the virus, for human transcriptomics changes related to SARS-CoV-2 related and as dried blood spots (DBS, which also inactivates the virus) for Mass cytometry (CyTOF) for B and T cell markers, and parasite and host genetics related to susceptibility to respiratory illness and COVID-19 infection. The serum will be used for SARS-CoV-2, related coronaviruses and malaria serology (IgG, IgM and IgA), and cytokine and chemokine panel assays. Full blood haematology and biochemistry will be performed on day 0 and day 28. Human transcriptomics, CyTOF and cytokine and chemokine assays will be carried out on the blood samples from healthy control participants. For more details about the laboratory assays, please see sections 16.9, Appendix IX. Description of other clinical and laboratory methods, page 118.

Should funds be available, the serological assays will be extended to include antibody responses to other potential coinfections, including hepatitis, respiratory pathogens such as respiratory syncytial virus, parainfluenza, *Klebsiella pneumoniae* and parasitic infections such as schistosomiasis, and soil-transmitted helminths. Additionally, whole blood will be run for molecular diagnoses on a TaqMan array card panel to evaluate for potential viral, bacterial and parasitic coinfections and for tuberculosis Quantiferon assay (see 10.2.4, HIV testing and TB testing, below).

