### 11.1.4 Screening study (cross-sectional survey source population)

A source population of 4,720 suspected cases (2,360 in each country) is required to recruit a cohort of 708 participants (354 per country). This assumes a SARS-CoV-2 test positivity rate of 20% across the two countries and eligibility of 75% among those testing positive ( $0.2 \times 0.75 \times 4,720 = 708$ ). If the average malaria RDT test positivity in the source population is 20% across both countries pooled, then 4,720 suspected cases would consist of 234, 710, 710 and 3066 MAL+/C19+, Mal+/C19-, MAL-/C19-, and MAL-/C19- participants. Such a sample size with a ratio of 4:1 malaria-negative: malaria-positive participants would provide 80% power to detect a 25% difference from 18.6% to 23.3%, allowing for a 30% sample size inflation relative to a crude analysis that does not adjust for confounding (effective sample size of 3,630), or a 26% difference from 18.6% to 23.4% allowing for 35% sample size inflation (effective sample size 3,495) (two-sided  $\alpha = 0.05$ ).

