#### 16.9.4 Immunological CyTOF B/Tcell assays & and OLINK screen

**Collaborating institutions and contact persons:** [name] and [name], The [name] laboratory, Department of Microbiology and Immunology, The Global Health Vaccine Accelerator Platform (GH-VAP) program, Systems Biology/Systems Immunology Consortium, [name], USA.

**Objective:** To determine differences in cell phenotypes and protein markers in individuals with COVID19 with and without malaria, and healthy controls with no active COVID19 or malaria, and if vaccinated, at least 4 weeks previously against COVID19.

**Rationale:** Cellular activation can be profound in both COVID19 and malaria infections, leading to specific expansion or downregulation of cell populations which can have major impacts on disease progression and resolution. New technology such as CYTOF and OLINK allows simultaneous assessment of multiple cellular and protein products from small quantities of whole blood. Recent studies using CYTOF analysis from COVID19 patients described specific downregulation and immunosuppression of cellular responses, specifically those associated with CD45+ T cells. Analysis of cellular response to malaria with CYTOF has shown effects on B cell populations, specifically CD11c B cell subsets. This study provides a unique opportunity to examine the effect of co-infection on B and T cell profiles and relate these with downstream protein biomarkers which have been shown to be affected by COVID19 infection.

**Sample size:** Approximately 180 patients and 100 healthy controls

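### Healthy controls are cleared of SARS-CoV-2 by an antigen test and absence of symptoms alone, so a person whose PCR makes them a cohort case can also be a control

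*Protocol*

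**What the plan says.** Three places in the protocol set the test criteria for controls, and they agree.

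- Section 9.1.2: controls "will be SARS-CoV-2 antigen RDT negative (nasal swab) and Plasmodium antigen-negative (finger prick) and will have no symptoms at the time". People identified retrospectively among those already screened are asked to repeat only the rapid tests.
- Section 2.2.4, footnote a: "A sub-group of participants who test negative by both SARS-CoV-2 antigen RDT and malaria RDT, and are feeling well, will be invited" to take part as controls.
- Section 10.2.2: about 100 controls "who test negative by SARS-CoV-2 antigen RDT during screening and are malaria RDT negative will have a 5 mL venous blood sample taken".

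The purpose is given in section 16.9.4, which refers to "healthy controls with no active COVID19 or malaria, and if vaccinated, at least 4 weeks previously against COVID19". Section 9.1.2 makes this group the comparator for both COVID-19 groups, with and without malaria.

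The case side uses a wider set of tests. Section 9.1.1 says: "If a participant tests COVID positive for any rapid antigen tests, GeneXpert, or PCR, the participant shall be enrolled". Section 6.2.2.1 accepts a positive molecular test on its own as laboratory confirmation, and section 9.2.1.1 accepts PCR or antigen.

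On the screening swab, footnote d of section 2.2.4 says: "Any default diagnostic swab performed by local health authorities is acceptable". Section 9.1 expects results within 18 to 48 hours, and footnote e warns that they can take more than a day.

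**The concern.** Cases and controls are separated by different tests. A positive PCR is enough to be a case, but a negative PCR is not needed to be a control. Someone who is well, antigen-negative and PCR-positive satisfies both rules as written, and fails the condition of no active COVID-19 in section 16.9.4.

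This is a realistic possibility. Controls come from the screening population, which under section 6.2.1.1 includes contacts of cases and high-risk groups. Feeling well is a weak filter there; section 7.3 notes: "Currently at least half of the COVID-19 cases identified in Kenya are asymptomatic". Section 16.9.1 treats qPCR as the standard diagnostic and makes the accuracy of point-of-care antigen tests a study question. Even so, the antigen test is the only SARS-CoV-2 test a control must pass.

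At stake is the uninfected reference for the CyTOF, Olink and transcriptional comparisons. Infected people in that reference pull it towards the patients and blur the contrast. The results alone would not show this unless PCR status were linked to the control samples.

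**Working it through.** **1. The definitions side by side.** Take a person with no symptoms, negative antigen RDT, negative malaria RDT and positive PCR.

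- Control rule (2.2.4 footnote a, 9.1.2, 10.2.2): met.
- Case rule (6.2.2.1, 9.1.1, 9.2.1.1): SARS-CoV-2 criterion met.
- Intended control state (16.9.4, no active COVID-19): not met.

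Antigen result and symptoms are known on Day 0, while the PCR result typically follows 18 to 48 hours later. Control blood can thus be taken before the result exists. No section says that a later positive removes the sample.

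**2. The plan's own positivity figure.** Section 11.1.4: "This assumes a SARS-CoV-2 test positivity rate of 20% across the two countries". With 75% eligibility, 0.2 × 0.75 × 4,720 = 708, which reproduces the cohort size. The four cells add up: 234 + 710 + 710 + 3,066 = 4,720. Reading the third cell as malaria-negative, SARS-CoV-2-positive (its printed label repeats that of the fourth), planned positivity in malaria-negative people is 710 / (710 + 3,066) = 18.8%. Both 20% and 18.8% cover people with and without symptoms.

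**3. Share of antigen-negative people who are PCR-positive.** With PCR prevalence p, antigen sensitivity Se against PCR, and antigen specificity taken as 100%:

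f = p(1 − Se) / [p(1 − Se) + (1 − p)]

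The protocol gives neither Se nor p among symptom-free people, so both are assumed over a range. Expected PCR-positives per 100 controls:

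| Prevalence p | Se 80% | Se 60% | Se 40% |
|---|---|---|---|
| 5% | 1.0 | 2.1 | 3.1 |
| 10% | 2.2 | 4.3 | 6.2 |
| 18.8% | 4.4 | 8.5 | 12.2 |
| 20% | 4.8 | 9.1 | 13.0 |

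Lowest cell: 0.05 × 0.2 / (0.05 × 0.2 + 0.95) = 0.010 / 0.960 = 1.0%. Highest cell: 0.20 × 0.6 / (0.20 × 0.6 + 0.80) = 0.12 / 0.92 = 13.0%. Even at the lowest cell, the chance of at least one PCR-positive among 100 controls is 1 − (1 − 0.0104)^100, or about 65%.

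**4. Effect on a mean difference.** Suppose each misclassified control carries a fraction k of the average shift seen in cases. The observed difference is then (1 − kf) times the true one. At k = 1 it shrinks by f, that is by 1% to 13% over the table. At k below 1 it shrinks by less; for example, k = 0.5 gives 0.5% to 6.5%.

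**The case against.** The strongest reply is that the pieces are already there. Section 16.9.4 states the required condition, and section 9.1.1 sends anyone PCR-positive to the cohort, so a control whose PCR turns positive is plainly a case. Dropping such a sample could be left to the SAP, which is not among the documents at hand. This carries some weight: one linking sentence would be enough. But the operative rule is written three times, and followed exactly it admits these people. That is a stated definition in conflict with its purpose, not a detail left for later.

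The reply is right that reach is limited. The cohort's immunology objective in section 4.2 compares patients with and without malaria, all enrolled as SARS-CoV-2 positive, and does not use the controls.

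A reader might infer four stronger things that the protocol does not support.

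- **That about 5 to 13 of 100 controls are infected.** This applies the 20% positivity of all comers to people who must be symptom-free. Section 7.3 gives the asymptomatic share of cases, and attributes it to targeted screening; it does not give prevalence among well people.
- **That contrasts shrink by the full contaminated percentage.** This needs misclassified controls to carry the average immune shift of cases. They are symptom-free and may be early, recent or low-load infections, so the percentage is better read as a ceiling.
- **That controls should also be malaria-PCR-negative.** The study defines malaria by RDT or microscopy (section 5 figure notes, 6.2.3.1), so the malaria-negative patient group can include PCR-only infections too. A stricter rule for controls alone would make the compared groups less alike.
- **That every call-back control must have a PCR.** Section 9.1.2 plans only rapid tests at call-back, so this would be a new procedure. Section 9.1.1 also accepts antigen results as definitive in Kenya, so a molecular result may not exist for every antigen-negative person.

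**Conclusion.** The concern holds as a conflict between definitions, whatever the prevalence or test sensitivity. The control rule admits people whom the case rule would enrol, and no step separates them once the PCR result arrives.

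Its size cannot be determined from the protocol. About 1 to 13 PCR-positives per 100 controls is illustrative: it rests on assumed antigen sensitivity of 40% to 80%, assumed PCR prevalence of 5% to 20% among symptom-free people, and perfect antigen specificity. The corresponding dilution of contrasts with controls is at most about the same percentage, provided infected controls differ from uninfected ones no more than the average case does. The effect is confined to the systems-immunology comparison of about 180 patients with 100 controls. The primary endpoints, the randomised comparison, the sample sizes and the contrasts by malaria status are untouched. It is worth correcting because the correction is cheap and must be in place before samples are assayed.

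**What to change.** In sections 9.1.2, 10.2.2, 16.9.4 and footnote a of 2.2.4:

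1. State that any control with a positive screening PCR or GeneXpert result is excluded from the control set before assay.
2. Draw the blood as planned, but hold the sample until that result is in.
3. Flag controls with no molecular result, including call-backs tested only by rapid tests, and repeat the control comparisons without them as a sensitivity analysis.

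Keep the malaria RDT criterion as it is, and do not make call-back PCR mandatory.

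The cost is a few drawn samples left unused, a short wait before batching, and linking of screening results where they exist. Section 16.9.4 already stores and batches the fixed blood for CyTOF, so holding samples fits the planned workflow.
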